**7.1.7. Compensation for participation:**

Participants will not be compensated for participation in assessment or treatment visits. All participants will be paid \$25 each time they get their blood drawn. Participants who choose to withdraw prior to study completion will receive compensation for blood draws that they have completed. Payment will be provided via a rechargeable MasterCard® ClinCard. The MasterCard® ClinCard is a debit card issued to the study participant. Funds are loaded onto card through the ClinCard website at [www.clincard.com](http://www.clincard.com). Only authorized users will be able to access the ClinCard website to add funds with a username and password. The ClinCard funds will be available to recipients within 1 business day and can be used as the participant chooses. The participant will be notified that their name, address and date of birth will be shared with a third-party (ClinCard) solely for the purposes of payment processing. This information will only be used for the administration of the payment and will be kept strictly confidential.

For veterans who are Texas residents and who live outside of the local area, reimbursement for mileage and meals will be provided. Car rental or airfare and lodging will also be provided at no cost to them. All other participants are required to pay for their own transportation to and from the clinic whenever they are scheduled to attend a visit.

**7.1.8. Treatment Procedures.**

PE for PTSD (Foa, Hembree, & Rothbaum, 2007) is an empirically supported behavioral therapy that utilizes exposure-based interventions to targets the psychological mechanisms (i.e., avoidance; maladaptive cognitive changes) thought to maintain trauma-related symptoms. A standard outpatient PE protocol (90 minute sessions, over 10 weeks) includes: a) providing a treatment rationale; b) providing psychoeducation on common reactions to trauma; c) teaching relaxed breathing; d) completing *in vivo* exposures; e.) conducting imaginal exposure; and f) facilitating emotional and cognitive processing for the trauma. With *in vivo* exposures, participants repeatedly and systematically approach realistically safe people, places, objects, and situations that they are currently avoiding. In imaginal exposures, participants repeatedly and systematically approach their trauma memory and related thoughts and feelings. PE serves as the foundation for both treatment conditions described. Ways in which PE for PTSD is being augmented for each condition in this study are outlined below. See Appendix A for the treatment manuals.

***Massed-Prolonged Exposure (Massed-PE)***

*Massed-PE will include all of components of the Massed-PE protocol at Fort Hood with two enhancements:*

*Project Remission: Maximizing Outcomes with Intensive Treatments for Combat-Related PTSD*

1. Increased Number of Treatment Sessions. The proposed Massed-PE treatment will include a 50% increase in the number of treatment sessions of PE (15 sessions, 90 minutes each). The participants will have 3 consecutive weeks to complete treatment; however, the treatment window may be extended another week if necessary.

2. Release from Duty. The Massed-PE treatment will allow additional time to complete out-of-session PE homework exercises on a daily basis. The daily Massed-PE schedule during weekdays will begin with a 90-minute individual PE treatment session. The final portion of each daily treatment session will involve planning and scheduling of the homework exercises to be completed throughout the remainder of the day. Participants will complete these daily homework sessions as outlined in the primary treatment manual (Foa et al., 2007) without additional feedback or assistance from a therapist. The prescribed daily individual homework will include (1) listening to the 90-minute audiotope of that day's PE session, (2) completing at least two 45-minute in vivo exposure exercises, and (3) practicing relaxed breathing exercises. The in vivo exposure exercise may take 1-2 hours if it involves traveling to and from a specific location (e.g., shopping mall, movie theater, restaurant, sporting event, etc.) alone or with another individual (e.g., spouse, friend, therapist, etc.). Therefore, the overall amount of time devoted to PE and related homework exercises on a daily basis for the Massed-PE treatment on weekdays is estimated to be 6 to 7 hours. On the two weekends that occur during the middle of the 3-week Massed-PE, participants will be instructed to complete all of the regular homework exercises. The one exception for the weekends is that the participants will only listen to the 45-minute imaginal exposure portion of the treatment session audiotope from the previous Friday's individual PE treatment session rather than the full 90-minute treatment session. This is the standard PE protocol for review of session audiotapes between spaced-PE treatment sessions. In addition, weekend in vivo exercises may require traveling longer distances and require more time than may be feasible during weekdays.

***Intensive Outpatient Program Prolonged Exposure (IOP-PE)***

*The IOP-PE will include the same primary treatment components as the Massed-PE protocol plus six augmentations to maximize outcomes and target military-relevant components not previously evaluated. Similar to the Mass-PE, participants will have 3 consecutive weeks to complete treatment; however, the treatment window may be extended another week if necessary.*

1. Clinic-Based Completion of Daily Homework Assignments. Participants in the IOP-PE arm will complete all of their homework assignments in the IOP clinic, with the exception of in vivo exposure exercises. Patients will be provided with a private clinic office listen to the 90-minute PE session audiotope. Listening to audiotapes of treatments sessions, especially the imaginal exposure portion, is considered to be a key component of PE therapy. However, this component can be emotionally difficult and it is sometimes avoided. Providing structure and support to listen to the audiotope in the clinic will help ensure the completion of this PE component. Participants will be encouraged to take notes while listening to the audiotope about any portion that is impactful to them or that they would like to discuss during the brief processing session to be held with a therapist immediately after reviewing the audiotope (see below). Pilot data using this approach has demonstrated that this requires only about 15 minutes of additional therapist time with the potential to significantly improve outcomes.

2. Brief Therapist Feedback Sessions. Therapists will provide two 15-minute feedbacks sessions. The first will be after in vivo exposure homework to review any difficulties or challenges that may have occurred and to plan for the next in vivo exercise. The second will be after the listening to the PE session audiotope to focus on cognitive and emotional processing of the session.

3. Enhanced Social Support. Participants will be asked to identify a support person to be involved in treatment. Some participants may decline to identify a support person; in these instances the participant will be allowed to remain in the study although this element of treatment will not be administered. If the patient identifies a spouse or other support person, and if the support person is available and willing to attend, they will be invited to participate in Session 2 of the IOP-PE to review (1) the overall rationale for PE, (2) the schedule and format of the IOP-PE, (3) the Common Reactions to Trauma handout, and (4) methods to provide social support for the completion of in vivo exercises. This session will be completed by telephone or video if the support person is at a remote location. The support person will not be a study participant; no data will be collected from the support person only for the research.

4. Top Three Traumas. The IOP-PE arm will specifically assess and treat the top three traumas rather than limiting the imaginal exposure to the single worst and most currently distressing trauma.

5. Graduated Imaginal Exposure. The imaginal exposure portion of the IOP-PE arm will start with the trauma reported by the patient to be the least difficult of the top three traumas. It will then progress gradually to the worst trauma.

6. Posttreatment Booster Sessions. The IOP-PE treatment will include three booster sessions (up to 1-hour in length) scheduled for 1 week, 3 weeks, and 7 weeks after the completion of treatment. Booster sessions will be conducted in-person for participants in the local area and by telebehavioral health for those who traveled to participate in the research

**Project Remission: Maximizing Outcomes with Intensive Treatments for Combat-Related PTSD**

study. The target of the booster sessions will be the maintenance and enhancement of treatment gains and the titration of in vivo exposure sessions into the patient's home environment.

While receiving treatment in the study through the 6-month follow-up assessment, participants will be asked not to work with another therapist or seek additional treatment for PTSD symptoms. Participants will also be asked not to change the dose or frequency of any medications they may have been prescribed for their posttraumatic stress symptoms as much as possible so that we can test the effect of the interventions rather than the effect of any change in medication.

**7.2 Drugs, Dietary Supplements, Biologics, or Devices. N/A****7.3. Study Procedures/Research Interventions.**

| Study Procedures                                                                                         | Base Line | Post-BL | Wk 1: Session 1 | Interim Assess #1 | Interim Assess #2 | Interim Assess #3 | Post-TX | 3-Mo FU | 6-Mo FU |
|----------------------------------------------------------------------------------------------------------|-----------|---------|-----------------|-------------------|-------------------|-------------------|---------|---------|---------|
| Informed Consent                                                                                         | X         |         |                 |                   |                   |                   |         |         |         |
| Randomization                                                                                            |           | X       |                 |                   |                   |                   |         |         |         |
| 1. Clinician Administered PTSD Scale (CAPS-5)                                                            | X         |         |                 |                   |                   |                   | X       | X       | X       |
| 2. PTSD Checklist-5 (PCL-5)                                                                              | X         |         |                 | X                 | X                 | X                 | X       | X       | X       |
| 3. Sheehan Disability Scale                                                                              | X         |         |                 |                   |                   |                   | X       | X       | X       |
| 4. Brief Inventory of Psychosocial Functioning                                                           | X         |         |                 |                   |                   |                   | X       | X       | X       |
| 5. Demographics & Military Service Characteristic                                                        | X         |         |                 |                   |                   |                   |         |         |         |
| 6. Combat-Related PTSD Beliefs Inventory                                                                 | X         |         |                 |                   |                   |                   |         |         |         |
| 7. History of Head Injuries                                                                              | X         |         |                 |                   |                   |                   | X       | X       | X       |
| 8. Health Questionnaire                                                                                  | X         |         |                 |                   |                   |                   | X       | X       | X       |
| 9. MINI -7.0 (Mini International Neuropsychiatric Interview for DSM-5) Psychosis and Mania modules only. | X         |         |                 |                   |                   |                   |         |         |         |
| 10. Alcohol Use Disorders Identification Test (AUDIT)                                                    | X         |         |                 |                   |                   |                   |         |         |         |
| 11. Deployment Risk and Resilience Inventory (DRRI-2) Subscales:                                         | X         |         |                 |                   |                   |                   |         |         |         |

## Project Remission: Maximizing Outcomes with Intensive Treatments for Combat-Related PTSD

|                                                             |   |  |  |   |   |   |   |   |   |
|-------------------------------------------------------------|---|--|--|---|---|---|---|---|---|
| - Combat Experience
- Post-battle Experiences            |   |  |  |   |   |   |   |   |   |
| 12. Depressive Symptoms Index-Suicidality Subscale (DSI-SS) | X |  |  | X | X | X | X | X | X |
| 13. Self-Injurious Thoughts and Behaviors Interview (SITBI) | X |  |  |   |   |   | X | X | X |
| 14. Patient Health Questionnaire-9 (PHQ-9)                  | X |  |  | X | X | X | X | X | X |
| 15. Generalized Anxiety Disorder Screener (GAD-7)           | X |  |  |   |   |   | X | X | X |
| 16. Veterans Rand 12-Item Health Survey (VR-12)             | X |  |  |   |   |   | X | X | X |
| 17. Dimension of Anger Reactions-5 (DAR-5)                  | X |  |  |   |   |   | X | X | X |
| 18. Conflict Tactics Scale - Revised (CTS2)                 | X |  |  |   |   |   | X | X | X |
| 19. Quick Drinking Screen (QDS)                             | X |  |  |   |   |   | X | X | X |
| 20. Response to Stressful Experiences Scale (RSES)          | X |  |  |   |   |   | X | X | X |
| 21. Life Event Checklist (LEC - 5)                          | X |  |  |   |   |   | X | X | X |
| 22. PTSD Diagnostic Scale for DSM-5 (PDS-5)                 | X |  |  |   |   |   | X | X | X |
| 23. DRRI-2 Post-Deployment Social Support subscale          | X |  |  |   |   |   | X | X | X |
| 24. Patient Health Questionnaire (PHQ)-15                   | X |  |  |   |   |   | X | X | X |
| 25. Trauma-Related Guilt Inventory (TRGI)                   | X |  |  |   |   |   | X | X | X |
| 26. Post-Traumatic Cognitions Inventory (PTCI)              | X |  |  | X | X | X | X | X | X |
| 27. Childhood Trauma                                        | X |  |  |   |   |   |   |   |   |

**Project Remission: Maximizing Outcomes with Intensive Treatments for Combat-Related PTSD**

|                                                                           |   |   |           |   |   |   |   |   |   |
|---------------------------------------------------------------------------|---|---|-----------|---|---|---|---|---|---|
| Questionnaire (CTQ)                                                       |   |   |           |   |   |   |   |   |   |
| 28. Insomnia Severity Index (ISI)                                         | X |   |           |   |   |   | X | X | X |
| 29. PROMIS Sexual Function and Satisfaction Measures                      | X |   |           |   |   |   | X | X | X |
| 30. PROMIS Sleep Disturbance and Sleep-Related Impairment short forms     | X |   |           |   |   |   | X | X | X |
| 31. Snoring, Tired, Observed, Blood Pressure (STOP) Sleep Apnea Screen    | X |   |           |   |   |   |   |   |   |
| 32. Fagerstrom Test for Nicotine Dependence (FTND)                        | X |   |           |   |   |   | X | X | X |
| 33. Fagerstrom Test for Nicotine Dependence – Smokeless Tobacco (FTND-ST) | X |   |           |   |   |   | X | X | X |
| 34. Credibility / Expectancy Questionnaire (CEQ)                          |   |   | Session 2 |   |   |   | X | X | X |
| 35. Independent Evaluator Blind Form                                      |   |   |           |   |   |   | X | X | X |
| 36. Blood for genetic biomarkers                                          |   | X |           | X | X | X |   |   |   |

**7.3.1 Collection of Human Biological Specimens:**

Blood will be collected prior to treatment, and during three of the sessions of the 3-week treatment phase for all participants in collaboration with the CAP-Biomarkers and Genomics Core to examine gene expression profile links with Intensive Outpatient Prolonged Exposure that may be predictive of treatment outcomes. A skilled phlebotomist will draw the samples. All blood samples will be collected at the study site.

**7.3.1.1 Laboratory evaluations and special precautions:**

All blood samples will be collected at the study site and then transported to the CAP Biomarkers and Genomics Core in the UTHSCSA Department of Psychiatry and Behavioral Sciences at the UT Health-Long School of Medicine in room 727F for processing and storage in accordance with the CAP Biomarkers and Genomics SOP. This location is monitored 24-7 by a wireless monitoring system on the Isensix system and has approval as a VA-Approved Tissue Bank. The study staff will be available to offer assistance if the participant is distressed at any point during any procedures.

**7.3.1.2 Specimen storage:**

Biological specimens will be coded with a digital bar code that can be linked to the study and subject only by key-codes maintained by the CAP Data Management and Biostatistics Core.

### 7.3.2 Data Collection.

**7.3.2.1 Instrumentation:** See the table at Section 7.3 above for a summary of the assessments and timing of administration. A description of each of the assessments can be found at the end of this protocol. Assessments will be administered in person whenever possible. However, in order to accommodate participant schedules and/or instances in which a participant does not reside in the local area at the time of a follow up assessment, we may collect full or partial assessments in person or via phone, telebehavioral health, or electronic data capture using a secure link to the encrypted STRONG STAR database. Assessments completed remotely will not include biospecimen collection. Reasonable efforts will be made to collect all data as described in this protocol, but we expect some participants may not be able to complete part or all of any given follow up assessment.

The following data collected at Baseline, Post-Treatment, and 3-Month Follow-up will contribute to a separate study titled *Hypertension Risk in Deployed OIF/OEF/OND Veterans* being conducted at Yale University School of Medicine by [name] under the Yale IRB approval number 1506015992 and UTHSCSA IRB approval number HSC20170630H: History of Head Injuries, Clinician Administered PTSD Scale (CAPS-5), PTSD Checklist-5 (PCL-5), Alcohol Use Disorders Identification Test (AUDIT), and Veterans Rand 12-Item Health Survey (VR-12). This data will only be shared if the participant consents to participate in the separate study.

Clinician Administered PTSD Scale (CAPS-5) data collected at Baseline, Post-Treatment, and 3-Month Follow-up will also contribute to a separate study titled *Neurobiological Predictors and Mechanisms In Exposure Therapy for PTSD* being conducted at Carl R. Darnall Army Medical Center (CRDAMC) and UTHSCSA under UTHSCSA IRB protocol number HSC20170714H. The Overall PI for HSC20170714H is [name] at Emory University. This data will only be shared if the participant consents to participate in the separate study.

**7.3.2.2 Data Storage and Access:** Data will be coded using an assigned number. Hard copies of data collected during treatment will be placed into a lock box which will be transported by car to University of Texas Health Sciences Center San Antonio (UTHSCSA) STRONG STAR offices by a STRONG STAR staff member who will place it into the locked cabinets at the STRONG STAR offices. Data will be entered into the STRONG STAR database on a secure UTHSCSA server (physically located at the UTHSCSA Advanced Data Center), by member of the research team. Electronic data will be stored, managed, and analyzed by the STRONG STAR – CAP Data and Statistics Core staff of the STRONG STAR consortium. The study activities accomplished by the CTVHCS employees will be reviewed and monitored by the CTVHCS IRB.

Every member of the Research Team will be trained and monitored about how to handle and protect both medical and research records. Furthermore, the Research Team strictly controls access to study data.

## 7.4 Statistical Consideration

**7.4.1 Sample Size Estimation.** The primary hypotheses are tests of treatment differences in pre-post means using the pre-treatment score as a covariate. Statistical power for the analysis of covariance with  $r = .50$  between baseline and post-treatment is .81 to detect a standardized mean difference of .35. An analysis of unadjusted pre-post difference scores with  $N = 100$  per group would have power = .80 for a standardized difference of about  $d = .40$ . Cohen (1988) defined  $d = .2$  as “small,” and  $d = .5$  as “medium.” The PCL-5 in our experience has a baseline standard deviation of about 15, and smaller differences than  $d = .35$  are unlikely to be clinically meaningful. For differences in diagnostic proportions (Hypothesis 2),  $N = 100$  gives power = .80 for a difference of about 20% (i.e., 45% vs. 65% or 50% vs. 70%). This is an odds ratio of about 2.3, roughly equivalent to Cohen’s  $d = .45$ . For bivariate correlations,  $N = 100$  has power = .88 to detect a medium  $r = .30$ .

### 7.4.2 Primary (i.e., primary outcome variables) and secondary endpoints.

The study aim is to evaluate the efficacy of IOP-PE relative to Massed-PE in the reduction of PTSD diagnoses and symptom severity (primary measures = CAPS severity score; PCL-5) and associated disability and psychosocial functioning (Sheehan Disability Scale; Brief Inventory of Psychosocial Functioning). Secondary endpoints include associated psychopathology (severity scores on measures of depression, general anxiety, anger, and PTSD-related cognitions).

### 7.4.3 Data analysis.

**7.4.3.1 General Statistical Considerations.**

Data will be entered into the STRONG STAR database on a secure UTHSCSA server meeting HIPAA requirements on an ongoing basis using specialized software that provides for double entry and numerous internal validity checks and produces regular reports on data flow to identify any ongoing recruitment issues. Prior to statistical analyses, data will be inspected for outliers, unusual distributions that suggest transformations such as log, and patterns of missing data. Data will be analyzed using the SAS statistical system (SAS 9.4).

Missing Data. An Intent-to-treat analysis will be used with a likelihood-based analysis method which is robust if data are missing at random. Outcome data will be collected on all participants randomized, even if they elect to end treatment or study participation. If a reasonable predictive model for missing data can be found and patterns of attrition suggest possible bias, the primary analyses will be supplemented with inverse propensity score weighting and multiple imputation (Hirano et al., 2003, Lunceford & Davidian, 2004). This approach will make it possible to perform sensitivity analyses (Allison, 2014; Dziura et al., 2013; Mallinckrodt et al., 2012). All analyses will be implemented in the latest release of SAS/STAT PROC MI in SAS version 9.4 with the inclusion of a new Not Missing at Random option (Demirtas & Schafer, 2003; Little, 2009; Enders, 2010).

Baseline Analyses and Sites. Randomization is expected to produce a high degree of similarity between treatment groups, but treatment groups will be compared at baseline to determine comparability on the outcome variables and to identify potentially important covariates that are not of primary interest in the hypotheses but relate to the outcome criteria. Baseline scores will be used as covariates. Differences between active duty or veteran status and interactions of status by treatment are not expected once relevant patient characteristics such as baseline severity are controlled, but preliminary analyses will consider the need to include site in the analysis designs.

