**7.4.3.2 Hypotheses and Specific Data Analysis Plans**

Hypothesis 1: The IOP-PE treatment will result in larger reductions than the Massed-PE treatment in clinician-assessed PTSD symptoms on the CAPS-5 and self-reported PTSD symptoms on the PCL-5 at the posttreatment, 3-month, and 6-month follow-up points.

Hypothesis 2: The IOP-PE treatment will result in a larger percentage of participants who no longer meet clinician-assessed PTSD on the CAPS-5 than the Massed-PE treatment at the posttreatment, 3-month, and 6-month follow-up points.

Hypothesis 3: The IOP-PE treatment will result in greater improvements than the Massed-PE treatment in functional outcomes on the Sheehan Disability Scale and the Brief Inventory of Psychosocial Functioning at the posttreatment, 3-month, and 6-month follow-up points.

The analysis method for Hypotheses 1-3 will be mixed effects regression models with repeated measures. The general linear mixed model is appropriate for dimensional measures that are approximately normally distributed such as the CAPS-5 and PCL-5 (Hypothesis 1) and measures of self-reported symptoms (Hypotheses 3). For diagnosis (Hypothesis 2), the generalized linear mixed model is appropriate specifying binomial error and a logit link function. Fixed effects are treatment (Massed-PE vs. IOP-PE), time (post-treatment, 3 & 6 month FU), and the interaction of treatment by time, with baseline level used as a covariate when available. Planned contrasts will be done to test the significance of pre-post change within each treatment. The primary tests for Hypotheses 1 and 3 will be the difference between treatments in these pre-post change scores. For Hypothesis 2, it is the difference in proportion remitted post-treatment (all participants have PTSD pre-treatment). Stability of outcomes will be examined by evaluating the significance of changes after treatment and comparing baseline to the follow-up scores in each treatment condition. It is hypothesized that similar improvements will be found in service members and veterans, but the study is not powered to detect significant noninferiority differences.

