evaluate overall symptom duration, distress, impairment, dissociative symptoms, and global ratings by the interviewer. Validation studies are nearly complete to establish the psychometric properties of the CAPS-5 and findings will be reported in peer-reviewed publications. This interview is very similar to its predecessor, the CAPS for DSM-IV, which has been considered the gold standard for evaluating PTSD and demonstrated good reliability and validity (Weathers, Keane, & Davidson, 2001). In addition to reflecting diagnostic changes for PTSD in DSM-5, the CAPS-5 differs from the CAPS in that frequency and intensity ratings for each symptom are no longer scored separately, so the severity rating for each item determines whether a symptom is present or not. Subscale scores are calculated by summing severity scores for items in the following PTSD symptom clusters: re-experiencing, avoidance, negative alterations in cognitions and mood, and hyperarousal. Scores  $\geq 25$  indicate a probable diagnosis of PTSD.

2. PTSD Checklist-5 (PCL-5): The PCL-5 (Weathers, et al., 2010) is a 20-item self-report measure update of the PCL designed to assess PTSD symptoms as defined by the DSM-5. The PCL-5 is currently available and has been shown to have good psychometric properties. The PCL-5 evaluates how much participants have been bothered by PTSD symptoms in the past month (for baseline and follow up assessments) or the past week (all interim assessments) as a result of a specific life event. Each item of the PCL-5 is scored on a five point scale ranging from 0 "not at all" to 4 ("extremely").
3. Sheehan Disability Scale: The SDS is a 3 item self-report measure designed to measure the extent to which three areas (work, social life, and home life/family responsibilities) in the individual's life are compromised by panic, anxiety, phobic, or depressive symptoms. The SDS is not to be used for diagnostic purposes, however, it may be used to supplement a mental health assessment by providing a summary of functional impairment.

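### The planned mixed model leaves the three in-treatment PCL-5 scores unused, so for participants who miss every outcome visit missing at random must hold given baseline and arm alone

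*Protocol*

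**What the plan says.** **Model.** Section 7.4.3.2 of the protocol sets out: "Fixed effects are treatment (Massed-PE vs. IOP-PE), time (post-treatment, 3 & 6 month FU), and the interaction of treatment by time". Baseline, where it exists, enters as a covariate and not as a repeated outcome. The interim assessments are not levels of time.

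**Data collected.** The schedule in section 7.3 marks the PCL-5 at baseline, at Interim Assessments 1 to 3, post-treatment, and at 3 and 6 months. The PHQ-9 follows the same pattern. The CAPS-5, the Sheehan scale and the psychosocial functioning inventory have no interim measurement. Section 16.0 gives the PCL-5 a past-month window at baseline and follow-up, "or the past week (all interim assessments) as a result of a specific life event".

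**Missing data.** Section 7.4.3.1 states: "An Intent-to-treat analysis will be used with a likelihood-based analysis method which is robust if data are missing at random". It also states: "Outcome data will be collected on all participants randomized, even if they elect to end treatment or study participation". Inverse propensity weighting and multiple imputation are added on a condition: "If a reasonable predictive model for missing data can be found and patterns of attrition suggest possible bias". Sensitivity analyses are introduced as something this conditional step makes possible, with a not-missing-at-random option in the imputation software.

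**Follow-up after stopping.** Section 10.0 schedules an evaluation soon after discontinuation and says participants will be contacted for follow-up whether or not they finish. Section 7.3.2.1 allows remote assessment but expects that some people will miss part or all of a follow-up assessment. No loss rate is given.

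**The concern.** A likelihood analysis is valid under missing at random only with respect to the data that enter it. Here those data are baseline, arm and whatever is observed at three later visits. For someone with none of the three, only baseline and arm remain. Yet the trial records PTSD symptoms three times during treatment, when people decide whether to continue.

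If those scores predict who is lost, and do so differently in the two arms, the specified model can attribute selective loss to treatment. Different patterns of loss are plausible. Under section 7.1.8, IOP-PE adds clinic-based homework, therapist feedback sessions, three traumas instead of one, and booster sessions after treatment. If participants with high scores are lost mainly from IOP-PE, the error favours IOP-PE, the direction of Hypothesis 1.

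The second part is the condition on the supplementary analyses. Inspecting attrition can show dependence on observed scores. It cannot show dependence on scores that were never observed, which is the case a not-missing-at-random analysis exists to address. The condition also leaves the decision to be made after the data are seen.

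**Working it through.** **1. The plan's own figure.** Inputs from section 7.4.1: d = .35, baseline to post-treatment correlation r = .50, 100 per group (stated there for the difference-score analysis and taken to apply here too). Two-sided alpha .05 is assumed.
- Residual SD in SD units: √(1 − .50²) = .866.
- Noncentrality: (.35 / .866) × √(100/2) = 2.86.
- Power: Φ(2.86 − 1.96) = .815, against .81 stated. The figure reproduces and is not in dispute.
- On the PCL-5 scale, with the protocol's SD of 15, the target is .35 × 15 = 5.25 points.

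**2. Who informs the model.**

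| Outcome visits attended | In the likelihood? | Interim PCL-5 used? |
|---|---|---|
| Post-treatment, with or without follow-up | Yes | No |
| Not post-treatment, but 3 or 6 months | Yes | No |
| None of the three | No | No |

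**3. Assumed loss.** Section 7.1.1 randomises 250, and the power statement uses 100 per group. If the gap is an allowance for loss, it is (250 − 200)/250 = 20%. The protocol does not say so; 20% is an assumption.

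**4. Size of the possible bias.** A large-sample simulation (150,000 participants per scenario) used SD 15 and a first-order autoregressive correlation giving r(baseline, post) = .50. Dropout could follow each interim assessment, with log-odds depending on the latest interim PCL-5 (slope 0.8 per SD where dependent). The data are then missing at random only if the interim scores are used. Maximum likelihood with unstructured covariance and baseline as covariate was fitted (a) to post-treatment, 3 and 6 months as in section 7.4.3.2, and (b) with the three interim scores added as outcomes. The true difference was 0. Entries are the estimated post-treatment difference in PCL-5 points; positive values favour IOP-PE.

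| Dropout mechanism | Dropout, Massed-PE / IOP-PE | (a), none return | (b), none return | (a), half return at 3 and 6 months | (b), half return |
|---|---|---|---|---|---|
| Completely random | 19% / 19% | 0.22 | 0.19 | −0.09 | −0.08 |
| High scorers leave, same in both arms | 20% / 20% | −0.20 | −0.21 | −0.02 | −0.02 |
| High scorers leave IOP-PE only; random in Massed-PE | 20% / 20% | 0.84 | −0.05 | 0.46 | −0.08 |
| High scorers leave both arms, more from IOP-PE | 14% / 27% | 0.68 | 0.09 | 0.34 | −0.02 |
| High scorers leave IOP-PE, low scorers leave Massed-PE | 20% / 20% | 1.76 | −0.02 | 1.11 | 0.03 |

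Simulation error is about 0.2 points. Because (a) and (b) share the same data, their difference is steadier. In the last three rows it is 0.89, 0.59 and 1.78 if none return, and 0.54, 0.36 and 1.09 if half return.

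- Range under (a): about 0.3 to 1.8 points, that is 0.34/5.25 = 6% to 1.76/5.25 = 34% of the target. The upper end is 1.76/15 = 0.12 SD.
- Return of half the dropouts cuts the bias by 37% (1.76 to 1.11) to 50% (0.68 to 0.34).
- At a true difference of 5.25, the same mechanism in both arms gives 5.09 (none return) and 5.10 (half return), an error of at most 0.2.

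**5. Second check.** A simpler single-visit covariance analysis (125 per arm; correlations baseline-post .5, baseline-interim .6, interim-post .75; all but the first assumed) gave biases of 0.6 to 1.2 points under arm-specific loss. Adding the interim score reduced them to about 0 and lowered the variance by 6 to 10%. The variance fell even when dropout was completely random.

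**The case against.** Much of the opposing case is right and limits the point.

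- **Who is excluded.** A reader might infer that anyone without a post-treatment score is dropped. The model has three outcome times, so a 3- or 6-month score keeps a participant in.
- **Early dropouts.** A reader might infer that people who leave treatment early are ignored, or that the analysis is not intent-to-treat. Sections 7.4.3.1 and 10.0 plan to assess them, and participants are compared by assigned arm. What remains is loss to assessment, which section 7.3.2.1 expects.
- **The trigger.** The simulated loss depends on observed interim scores. In a reconstruction, a simple comparison of interim scores between dropouts and completers was significant in about 98% or more of simulated trials. If interim scores are inspected, the planned weighting and imputation would probably be prompted and could use them. It would be wrong to say the trigger offers no protection. It cannot detect dependence on unobserved scores, and the protocol does not say that interim scores will be inspected or used.
- **Assumptions.** The loss rate, mechanism and interim correlations are not in the protocol, and the bias disappears if loss works the same way in both arms.
- **Scope.** Only the PCL-5 (among the main outcomes) is measured during treatment, and its past-week window is a plausible reason not to treat it as an interchangeable repeat.
- **Left to the SAP.** Imputation variables and delta values may be fixed in an analysis plan not shown here. The time levels of the primary model and the condition on the supplementary analyses are fixed in the protocol, so the point does not rest on absent detail.

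**Conclusion.** The point holds in a limited form. As specified, the model does not use the three in-treatment PCL-5 scores, and participants missing all of post-treatment, 3 months and 6 months contribute nothing. Under about 20% loss that depends on in-treatment symptoms differently by arm, the PCL-5 difference could be biased by roughly 0.3 to 1.8 points against a target of 5.25. The lower part of that range applies if half of those lost return for follow-up. With the same mechanism in both arms the bias is about zero.

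A reader might infer that the trial's result will be biased. The documents do not support that: they give no loss rate and no sign of arm-specific loss. The size for CAPS-5, diagnosis and functioning was not computed. The case for change is that the interim scores are already collected, that using them removes this possible bias and improves precision, and that a sensitivity analysis for unobserved dependence should not wait on observed attrition. The change should be made, but the trial is not invalid without it.

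**What to change.** 1. **PCL-5 model (7.4.3.2).** Add Interim Assessments 1 to 3 as separate time levels with unstructured covariance, keeping baseline as covariate and the primary contrast at post-treatment. Alternatively, use the interim scores as auxiliary variables. Six time levels need 6 × 7/2 = 21 covariance parameters; name a fallback structure in case of non-convergence.
2. **CAPS-5, diagnosis and functioning (7.4.3.1).** Prespecify multiple imputation of all randomised participants, with interim PCL-5 and PHQ-9 as auxiliary variables, and remove the condition on observed attrition.
3. **Sensitivity analysis (7.4.3.1).** Commit to one not-missing-at-random analysis, for example delta-adjusted imputation, whatever the attrition pattern.

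The cost is some programming and rewording of two subsections; no new data are needed. The interim PCL-5 has a shorter recall window than the other visits. Separate time means and an unstructured covariance accommodate this, because the interim scores then inform the post-treatment contrast only through their correlation with it.
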